Evidence from interventions designed to enhance the maintenance of physical activity, diet and weight loss suggests the importance of extended intervention contact after initial intervention [14,16,17]. Extended contact provides the opportunity to reinforce behavioural skills learnt during the initial intervention, support problem solving and provide continued accountability and motivation. A recent meta-analysis of randomised controlled trials (n = 11) of extended contact interventions for weight loss maintenance concluded that they are viable and efficacious [17]. Common features of successful extended contact interventions for weight loss maintenance include: contact from interventionists (rather than peers or non-interventionist contact); and, reinforcement of behavioural skills, particularly support for setting and meeting behavioural goals, problem-solving skills and training in relapse prevention [17]. Previous trials have primarily evaluated extended contact interventions delivered via face-to-face group or individual sessions [18-20], although it has also been shown that face-to-face session attendance decreases as treatment duration approaches one year and as individuals regain weight [14,21]. Some trials have found telephone-delivered extended contact interventions lead to better weight outcomes for participants compared to control groups [21-23]. There is mixed evidence supporting the efficacy of web-based extended contact interventions for weight loss and behaviour change [24], with poor results being attributed to the lack of active and ongoing engagement of participants with the website.

Mobile telephone text messaging may be particularly suited as a delivery modality for extended contact interventions. Text messages can: efficiently deliver tailored repeated contacts from interventionists; be actively “pushed” to participants to maintain contact over long periods of time; prompt behaviours and use of behavioural skills in real time; and, maintain two-way communication with an interventionist using minimal resources. Evidence is rapidly emerging supporting the efficacy of text message-delivered interventions to promote initial weight loss, physical activity and dietary behaviour change [25-30]. Recently, a small (n = 34), pilot trial reported continued weight loss from participants receiving a text message-delivered extended contact weight loss intervention [31]. This area of research holds great promise and requires ongoing investigation.

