### Control group treatment

The control group receives no contact, except for the evaluations at baseline, 6- and 12-months. Following completion of each assessment, control group participants are posted brief written feedback on their results to reduce attrition.

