### Statistical analysis

#### Intervention effects

Data will be analysed using intention-to-treat principles (i.e., participants will be analysed according to their randomly assigned group, regardless of the amount of intervention received). Each primary outcome will be modelled using mixed linear models with random intercepts, the fixed effects of study group, time (6-months/12-months) and a group by time interaction and will adjust for baseline values and potential confounders. Depending on the distribution of the continuous, interval or categorical outcome an appropriate distribution (e.g. normal, log-normal, gamma, negative binomial, binomial) and link (e.g., identity, logit) will be used. These models will assess intervention effects at end-of-intervention (6-months), end-of-maintenance (12-months) as well as differences between end-of-intervention and end-of-maintenance. Potential confounders include baseline demographic, behavioural and health characteristics as well as pre-intervention weight loss and behaviour changes. Those variables associated with the outcome at p < 0.2 will be adjusted as potential confounders. Final models will include all these potential confounders or remove those that do not affect estimates to within ±20% if models show evidence of overfitting. Sensitivity of conclusions to assumptions regarding missing data will be evaluated by comparing results obtained using different techniques of handling missing data (completers analysis, covariate adjustment and multiple imputation).

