### Sample size

The estimated differences between groups in change in primary outcomes (and standard deviations) for this trial are based on the outcomes from the maintenance evaluation of the GHS from 6 to 12 months without ongoing contact (same as control group treatment in the current study) [34] and literature on change in anthropometric and behavioural outcomes during extended contact interventions [17,18,31]. This evidence shows that we can expect small, continued improvements in the GHSH group from baseline to 6 months and declines in the no contact control group. Based on this, the minimum differences of interest in changes between groups from baseline to 6 months for our primary outcomes are: 2 sessions/week of self-reported moderate-vigorous physical activity; 1 serve of fruit per day and 1 serve of vegetables per day; 2 kg body weight; and, 4 cm waist circumference. The sample size requirement was largely determined by self-reported physical activity (sessions/week) as this outcome required the largest number of participants. Allowing for an attrition rate of 20%, the targeted sample size of 106 participants per group (212 in total) is needed to provide a ≥90% power with 5% significance (two-tailed) to detect a between group difference in change of 2 sessions per week of moderate-vigorous physical activity (assuming a standard deviation (SD) of 5.7sessions/week [34] and pre-post correlation (r) of 0.70 [unpublished data]). It is estimated, based on previous evaluations of GHS [34, unpublished data], that this sample size also provides ≥90% power to detect minimum differences of interest in all other primary outcomes including fruit serves/day (assumed SD = 0.9, r = 0.40), vegetable serves/day (assumed SD = 1.5, r = 0.37), weight in kilograms (assumed SD = 16.5, r = 0.97) and waist circumference in centimetres (assumed SD = 13.5, r = 0.80); as well as our additional measures of physical activity (accelerometer-measured moderate-vigorous physical activity minutes/week (assumed difference = 60, SD = 147, r = 0.60) [75]); and dietary behaviours (FFBQ Total Index (assumed difference = 0.20, SD = 0.50, r = 0.70 [76]).

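### The missing-data sensitivity comparison uses only methods that ordinarily assume missing at random or stronger, so agreement among them cannot show robustness to dropout driven by unobserved outcomes

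*Protocol article*

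**What the plan says.** The Intervention effects section of the Protocol article gives a purpose: "Sensitivity of conclusions to assumptions regarding missing data will be evaluated". The means is "comparing results obtained using different techniques of handling missing data (completers analysis, covariate adjustment and multiple imputation"). The list is closed, and no departure from MAR is mentioned.

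The primary analysis in the same section uses "mixed linear models with random intercepts, the fixed effects of study group, time (6-months/12-months) and a group by time interaction", adjusted for baseline values and potential confounders.

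Three other statements bear on the point:
- Sample size: "Allowing for an attrition rate of 20" per cent, with an expectation of "small, continued improvements in the GHSH group from baseline to 6 months and declines in the no contact control group".
- Control group treatment: "The control group receives no contact, except for the evaluations at baseline, 6- and 12-months". Controls are also posted written feedback after each assessment to limit attrition. The intervention arm receives text messages and two tailoring calls over the first 6 months.
- Background: in earlier extended-contact trials "face-to-face session attendance decreases as treatment duration approaches one year and as individuals regain weight". The same section gives an average regain of 0.3 kg per month after an intervention ends.

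**The concern.** A sensitivity analysis for missing data is useful only if it varies the assumption that could be wrong. Completers analysis needs MCAR, or missingness that depends only on covariates in the model. Covariate adjustment and ordinary multiple imputation need MAR. So does the likelihood-based mixed model. Because baseline enters that model as a covariate, a participant seen at neither follow-up contributes no outcome to it.

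If people leave because of a 6-month outcome that nobody records, all four analyses can be wrong by a similar amount and still agree. The trial would then report robustness it had not tested. Contact differs by arm during the first 6 months, so there is no assurance that such dropout would be the same in both arms and cancel.

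**Working it through.** **Inputs from the Sample size section.** Weight SD 16.5 kg, correlation 0.97, difference of interest 2 kg, 106 per group, attrition 20%. From Background: 0.3 kg per month average regain.

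**The plan's own figure.** No stated figure measures the missing-data problem. The related one is the sample size. For physical activity, the baseline-adjusted SD is 5.7 × √(1 − 0.70²) = 4.07 sessions per week. A 2-session difference at 90% power and two-sided 5% needs 88 per group, and 88 × 1.20 = 105.6, rounded up to 106. This reproduces the target. Completers per arm at 20% loss are 106 × 0.8 = 84.8.

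**Precision for weight at 6 months.** Residual SD = 16.5 × √(1 − 0.97²) = 4.01 kg. SE of the difference = 4.01 × √(2/84.8) = 0.616 kg. Significance needs about 1.96 × 0.616 = 1.21 kg.

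**Do the three methods respond to outcome-dependent dropout?** Simulation of the 6-month weight comparison: 400,000 participants per scenario, true difference −2.0 kg, about 20% dropout overall. Assumptions not in the documents: mean baseline weight 85 kg, mean control gain 1 kg, and a dropout log-odds slope of 0.3 per kg of weight change (rows 1 to 3) or an analogous dependence on baseline weight (rows 4 and 5). Estimates in kg:

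| Dropout depends on | Completers | Covariate-adjusted | Imputation under MAR |
|---|---|---|---|
| Unobserved 6-month change, both arms | −1.71 | −1.72 | −1.72 |
| Unobserved 6-month change, intervention only | −2.82 | −2.81 | −2.81 |
| Unobserved 6-month change, control only | −0.99 | −1.00 | −1.00 |
| Baseline weight, both arms | −1.99 | −1.99 | −1.99 |
| Baseline weight, intervention only | −2.11 | −2.00 | −2.00 |

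In the first three rows the methods agree to within 0.01 kg and share a bias of about 0.3 to 1.0 kg. Only the last row, where dropout is MAR, separates them.

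**What a delta adjustment would show.** Shift in the difference = (share missing in intervention × delta in intervention) − (share missing in control × delta in control).
- Intervention dropouts only, 0.3 kg per month beyond the MAR prediction: 0.20 × 0.3 × 6 = 0.36 kg at 6 months (18% of 2 kg), and 0.20 × 0.3 × 12 = 0.72 kg at 12 months (36%). The 12-month figure is a maximum, because it needs all dropout to occur straight after baseline.
- 4 kg in intervention dropouts only, 20% missing: −2.0 + 0.8 = −1.2 kg. In control dropouts only: −2.0 − 0.8 = −2.8 kg. In both arms: no change.
- 4 kg in both arms, 30% missing in intervention and 10% in control: −2.0 + 1.2 − 0.4 = −1.2 kg.

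**Would conclusions change?** With the SE held at 0.616:
- A 2 kg estimate survives both illustrative shifts: 1.64/0.616 = 2.66 and 1.28/0.616 = 2.08.
- Its tipping point, for intervention dropouts only, is (2 − 1.21)/0.20 ≈ 4.0 kg for loss of significance and 2/0.20 = 10 kg for a null estimate.
- A smaller estimate tips sooner. A shift of 0.36 kg removes significance from estimates between about 1.21 and 1.57 kg, and 0.72 kg does so up to about 1.93 kg. Applying the 6-month SE to the 12-month shift is an approximation.

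**The case against.** The strongest reply is that a condensed article gives missing data one sentence, names multiple imputation without its model, and leaves the rest to an analysis plan. Imputation can be run under a missing-not-at-random model, and a plan not shown here might do so. That would answer a complaint about missing detail. It does not fully answer this one, because the article states an aim and a closed list of methods, and the list as ordinarily run does not reach the aim.

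Three stronger readings are tempting, and the documents do not support them.

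- A reader might infer from Background that regain-driven dropout is likely. That statement concerns attendance at face-to-face treatment sessions. Outcomes here come from telephone interviews, posted questionnaires and posted accelerometers. Missing a session is not the same as being lost to assessment, so the link is indirect and plausible is the fair word.
- A reader might infer that the comparison is worthless. It is not: setting completers against imputation does contrast MCAR with MAR. Baseline and pre-intervention change are also candidate covariates, and regain recorded at 6 months before dropout by 12 months is MAR for the mixed model. The gap is regain never observed, mainly at 6 months.
- A reader might take 0.36 and 0.72 kg as the expected bias, or assume it favours the intervention. The 0.3 kg per month is an average regain, not an excess among dropouts, and nothing in the documents places it in one arm. The feedback sent to controls is meant to limit attrition, and neither arm has intervention contact after 6 months.

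**Conclusion.** The concern holds in limited form. The listed methods, as ordinarily run, can tell MCAR from MAR but cannot test dropout driven by unobserved outcomes, so their agreement is not evidence of robustness to it. The size is unknown from the documents. The 0.36 kg and at most 0.72 kg shifts rest on 20% missing in the intervention arm, excess regain at 0.3 kg per month, and no excess in control. Direction is open: in the simulation, equal dependence in both arms weakened the effect, dependence in the intervention arm alone inflated it, and dependence in control alone roughly halved it. If the trial observes the full 2 kg difference, the illustrative range would not overturn significance. For a smaller estimate it could, and the planned comparison would not reveal this.

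**What to change.** Keep multiple imputation under MAR as the reference and add a delta-adjusted (pattern-mixture) multiple imputation for each primary outcome.

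- Vary delta separately by arm and in both directions.
- Widen it until the conclusion changes, and report that tipping point. For weight, a range ending at 1.8 kg (6 months) or 3.6 kg (12 months) would stop short of the roughly 4 kg needed to tip a 2 kg estimate.
- For weight, use 0.3 kg per month as an illustrative step, labelled as an assumption.
- For the other outcomes, scale delta to the minimum differences in the Sample size section: 2 sessions per week, 1 serve per day each of fruit and vegetables, and 4 cm waist. For the additional measures, use the assumed differences of 60 minutes per week by accelerometer and 0.20 on the dietary index.
- State that agreement among the three existing methods addresses MCAR against MAR only.

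The cost is extra imputation runs and one supplementary table per outcome, with more care where an outcome is modelled as non-normal. It needs no new data and leaves the primary analysis unchanged.

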#### Secondary analyses

Feasibility and acceptability outcomes will be reported descriptively. Mediation and moderation analyses will be exploratory. The extent to which theoretically-driven constructs and mechanisms for behaviour change mediate the intervention effects will be examined using a simple product-of-coefficient approach using Sobel tests [74]. Point estimates and bootstrap confidence intervals of path coefficients and the product of the mediated path coefficients will be used to determine the potency, certainty and direction of any mediation effect [74]. Moderator analysis will examine whether variation of intervention effects differ across demographic characteristics, health status and pre-intervention weight loss/behaviour change (i.e. during initial GHS). These analyses will test intervention effects (as above) but using interaction terms to allow the effects of group, time and group by time to also vary by each moderator. These models will assess moderation of end-of-intervention, end-of-maintenance as well as differences in moderation between these periods.

### Sample size

The estimated differences between groups in change in primary outcomes (and standard deviations) for this trial are based on the outcomes from the maintenance evaluation of the GHS from 6 to 12 months without ongoing contact (same as control group treatment in the current study) [34] and literature on change in anthropometric and behavioural outcomes during extended contact interventions [17,18,31]. This evidence shows that we can expect small, continued improvements in the GHSH group from baseline to 6 months and declines in the no contact control group. Based on this, the minimum differences of interest in changes between groups from baseline to 6 months for our primary outcomes are: 2 sessions/week of self-reported moderate-vigorous physical activity; 1 serve of fruit per day and 1 serve of vegetables per day; 2 kg body weight; and, 4 cm waist circumference. The sample size requirement was largely determined by self-reported physical activity (sessions/week) as this outcome required the largest number of participants. Allowing for an attrition rate of 20%, the targeted sample size of 106 participants per group (212 in total) is needed to provide a ≥90% power with 5% significance (two-tailed) to detect a between group difference in change of 2 sessions per week of moderate-vigorous physical activity (assuming a standard deviation (SD) of 5.7sessions/week [34] and pre-post correlation (r) of 0.70 [unpublished data]). It is estimated, based on previous evaluations of GHS [34, unpublished data], that this sample size also provides ≥90% power to detect minimum differences of interest in all other primary outcomes including fruit serves/day (assumed SD = 0.9, r = 0.40), vegetable serves/day (assumed SD = 1.5, r = 0.37), weight in kilograms (assumed SD = 16.5, r = 0.97) and waist circumference in centimetres (assumed SD = 13.5, r = 0.80); as well as our additional measures of physical activity (accelerometer-measured moderate-vigorous physical activity minutes/week (assumed difference = 60, SD = 147, r = 0.60) [75]); and dietary behaviours (FFBQ Total Index (assumed difference = 0.20, SD = 0.50, r = 0.70 [76]).

## Discussion

Extended contact following behavioural weight loss interventions is considered best practice for the maintenance of weight loss [17]. Text messaging may offer an ideal medium to deliver this extended contact. The Get Healthy, Stay Healthy (GHSH) trial will evaluate the feasibility, acceptability, efficacy, mediators and moderators of weight loss maintenance and behaviour change of a text message-delivered extended contact intervention following completion of the GHS - a population-based telephone-delivered healthy lifestyle program. A recent review of the evidence for extended contact interventions [17] recommended that future research identify dose-responsiveness of extended contact, exploit the strengths of mediated delivery modalities (e.g. real-time prompting by handheld devices), and examine the maintained effect of extended contact. The present study is responsive to this call and will also examine dose-responsiveness, maintenance and report on intervention delivery costs.

In the broader context of population-based weight loss and behaviour change programs (and in a context of scarce health care resources) funding agencies have practical questions that go beyond intervention effectiveness, including: How long do effects last and for how long it is necessary to deliver the intervention?; For whom does the intervention work?; and, Could it be delivered in a shorter and/or more cost-effective format? There is a paucity of research that speaks to these issues, all of which are important in informing uptake, implementation and sustainability of such programs delivered in real world, up-scaled population health contexts. Our research partners, the New South Wales Ministry of Health, recognise the critical importance of maintaining program outcomes to validate their ongoing expenditure on the GHS. The current study, with its rigorous methodology, has the capability not only of informing future service delivery of the GHS but also contributing to the broader evidence base on cost-effective means of promoting weight loss maintenance and multiple health behaviour change.

## Abbreviations

GHS: Get Healthy Information and Coaching Service; GHSH: Get Healthy, Stay Healthy; CATI: Computer-assisted telephone interview; FFBQ: Fat and Fibre Behaviour Questionnaire.
